### Participants

Participants comprise families of children aged 8–12 years with diagnostically-confirmed ADHD (see inclusion criteria) who also meet diagnostic criteria for one or more of Separation, Generalized, and Social Anxiety Disorder.

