### Measures

This project uses REDCap to collect survey and interview data from parents, children and teachers. Study measures are summarized in Table 2. The primary outcome is whether the child meets diagnostic criteria for one or more anxiety disorders (Separation, Social or Generalized Anxiety Disorder) measured by the Anxiety Disorders Interview Schedule for Children V at 5 months post-randomization [27]. This measure has been selected as it is rigorous, maps onto DSM criteria, and takes into account both anxiety symptom severity *and* impairment. This interview is administered by an assessor unaware of group allocation via telephone with a parent/carer parents [42]. The diagnostic interview is repeated at 12 months post-randomization.

**Table 2 Tab2:** Study measures

Construct	Measure	Source^a^	T1^b^	T2^c^	T3^d^
Primary Outcome					
Anxiety diagnoses	*Anxiety Disorders Interview Schedule for Children V:* Separation, Social, & Generalised Anxiety Disorder [27].	P	x	x	x
Secondary Outcomes					
Anxiety symptoms and impact	*Spence Children’s Anxiety Scale:* Child (44-item) and parent (38-item) reported anxiety symptoms [31].	P, C	x	x	x
	*School Anxiety Scale:* 16-items assessing anxiety symptoms at school [32].	T	x	x	x
	*Child’s Anxiety Life Interference Scale:* Child (9-items) and parent (16-items) report [33].	P, C	x	x	x
ADHD	*ADHD Rating Scale IV:* 18-item validated scale measuring the core symptoms of ADHD [26].	P, T	x	x	x
Behavior	*Strengths and Difficulties Questionnaire:* 25-items assessing child behavior and peer problems [34].	P, T, C	x	x	x
Irritability	*Affective Reactivity Index*: A 6-item validated measure assessing child irritability [35].	P	x	x	x
QoL	*Child Health Utilities Index Nine Dimension*: Preference-based measure of health-related QoL [36, 37].	P, C	x	x	x
Sleep	Single item primary caregiver report of whether the child’s sleep is a problem (none, mild, moderate or severe) [38].	P	x	x	x
School attendance	Number of days late/missed [38].	P	x	x	x
Cognitive function	*NIH Toolbox Cognition Battery:* Computer- administered assessment of cognitive and executive function, attention, episodic/working memory, and processing speed [39].	D	x	x	x
Parent mental health	*Kessler 6 (K6):* A 6-item validated measure of adult psychological stress resulting in a total score range from no distress to severe distress [40].	P	x	x	x
Parenting	*Parenting behavior:* Scales assessing parenting consistency (6-items) and warmth (6-items) [41].	P	x	x	x

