### Data analysis

Primary analyses will follow the ‘intention to treat’ principle at the child level. To account for loss to follow-up, analysis of the primary outcome (presence of Separation, Social and/or Generalised Anxiety Disorder) and all secondary outcomes will be carried out using mixed effects regression. For each outcome, a single mixed effects model will be fitted incorporating baseline, 5 month and 12 month data, adjusted for gender (randomization stratification factor), using random effects to allow for the repeated measures within an individual. These models will fit separate random effects and error terms at each time point, and a separate fixed effect of treatment at each of the two post-randomization time points. This approach implicitly deals with missing data as it enables all participants with baseline data to be included in the analysis.

For the primary outcome and other binary outcomes, groups will be compared using mixed effects logistic regression, with results presented as odds ratios and their 95% confidence intervals [CI] at 5 and 12 months. For continuous and count data secondary outcomes, groups will be compared using linear or Poisson mixed effects regression, as appropriate, with results presented as mean differences (and 95% CIs) in outcomes at 5 and 12 months. In addition, we will repeat the analysis adjusted for baseline covariates as appropriate: for example, child sex (male, female), child age, medication use (yes/no), comorbidities (yes/no), therapist, and family socioeconomic status). For our primary outcome, whether the child meets criteria for an anxiety disorder (separation, social or generalised anxiety diagnosis) at 5 months, a sensitivity analysis will be conducted using multiple imputation to handle the missing data with analysis via logistic regression applied to the 5 month data only.

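### The primary outcome gets no adjustment for baseline anxiety: its model carries sex only, every child has the diagnosis at entry, and the baseline severity scores go unused

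*Protocol article*

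**What the plan says.** All references are to the protocol article.

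- **Model (Data analysis).** For each outcome, "a single mixed effects model will be fitted incorporating baseline, 5 month and 12 month data", and this model is "adjusted for gender (randomization stratification factor", with random effects for the repeated measures on each child. It includes "a separate fixed effect of treatment at each of the two post-randomization time points", so the arms share one baseline mean. The primary outcome uses the logistic form.
- **Missing data (Data analysis).** The justification given is: "This approach implicitly deals with missing data as it enables all participants with baseline data to be included in the analysis".
- **Adjusted repeat (Data analysis).** A supplementary analysis adds covariates where appropriate. Besides sex, the examples are "child age, medication use (yes/no), comorbidities (yes/no), therapist, and family socioeconomic status".
- **Eligibility (Participants).** The children have ADHD and are those "who also meet diagnostic criteria for one or more of Separation, Generalized, and Social Anxiety Disorder". The Measures section defines the primary outcome by the same three disorders on the same interview.
- **Baseline severity (Measures, Table 2).** The Spence Children's Anxiety Scale is collected at baseline: "Child (44-item) and parent (38-item) reported anxiety symptoms". The Child's Anxiety Life Interference Scale is also collected then.
- **Order of events (Randomization).** Baseline parent and child measures are completed before allocation, which is stratified by sex only.

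**The concern.** One modelling template serves every outcome, but it does different things for different outcomes. With a continuous scale, the baseline value varies between children and is correlated with follow-up, so including it as a repeated measure adjusts for it. With the primary outcome, every child is a case at baseline, so the baseline record cannot separate a mild case from a severe one.

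Baseline severity is a natural candidate predictor of still having a diagnosis at 5 months, yet it has no named place in any analysis of the primary outcome. Three things are at stake:

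- power for the main comparison;
- exposure of the estimate to chance imbalance in severity, which stratifying by sex does not control;
- the missing-data argument, which relies on baseline information that the primary model does not hold.

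**Working it through.** **1. The plan's own sample size.** Inputs from the Sample size section: remission 40% versus 20%, two-sided alpha 0.05, power 80%, drop-out 20%.

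- Uncorrected: n = [1.96·√(2·0.3·0.7) + 0.842·√(0.4·0.6 + 0.2·0.8)]² / 0.2² = 81.2, so 82 per arm.
- With continuity correction: n = (81.2/4)·[1 + √(1 + 4/(81.2·0.2))]² ≈ 91 per arm.
- With drop-out: 91/0.8 = 113.75, so 114 per arm and 228 in total, as stated.
- Odds ratio: (0.4/0.6)/(0.2/0.8) = 2.67, as stated.

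At 91 analysed per arm, power without continuity correction is 84.3%. This is the reference for step 3.

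**2. Does the baseline record inform the primary model?** With time as a factor, a child's baseline likelihood term is P(Y₀ = 1 | u) = 1/(1 + exp(−(m₀ + u))), where u is the random effect. Since Y₀ = 1 for all, the likelihood is maximised as m₀ → ∞. The term then equals 1 for every u and drops out.

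A numerical check used a simulated data set (91 per arm, random-intercept logistic model, 40-point quadrature, sex omitted for simplicity):

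| | Without baseline record | With baseline record |
|---|---|---|
| 5-month log OR for diagnosis | −2.2048 | −2.2048 |
| 12-month log OR for diagnosis | −1.8241 | −1.8241 |
| log SD of random effect | 0.7617 | 0.7617 |
| Minus log-likelihood | 206.7542 | 206.7542 |
| Baseline intercept | – | diverges (above 20) |

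The baseline record adds nothing, and a child with baseline data only adds nothing to the treatment estimate.

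**3. Power with a severity covariate.** The article gives no association between severity and remission, so its strength is an assumption shown as a range. Method: logistic regression on 5-month data, 91 per arm, intercepts solved so that marginal remission is 20% and 40%, 6,000 replicates.

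| Assumed OR per SD of severity | Power, unadjusted | Power, adjusted | Conditional treatment OR |
|---|---|---|---|
| 1.5 | 84.4% | 85.3% | 2.75 |
| 2.0 | 84.6% | 87.7% | 2.92 |
| 2.5 | 83.6% | 88.1% | 3.11 |
| 3.0 | 83.3% | 90.3% | 3.29 |

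Separate runs of 1,500 and 4,000 replicates agree. At an OR of 3.7 per SD they gave 85% versus 92% and 85% versus 93%.

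**4. Chance imbalance.** The arm difference in mean standardised severity has standard error √(2/91) = 0.148 SD, so 95% of trials fall within ±0.29 SD. At an assumed OR of 2 per SD, the edge of that range shifts the log odds ratio by roughly 0.29 × ln 2 = 0.20, a factor of about 1.22. The unadjusted confidence interval covers this on average, but adjustment would remove it in the trial at hand.

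**5. Missing data.** Assume 20% drop-out in each arm, rising with severity in the CBT arm (OR 1.5 to 3 per SD) but unrelated to severity in controls, and severity lowering the odds of remission by the same range. Observed CBT remission is E[p(x)w(x)]/E[w(x)], with w(x) the probability of being observed.

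- Weakest case: 0.4073, giving (0.4073/0.5927)/0.25 = 2.75.
- Strongest case: 0.4377, giving (0.4377/0.5623)/0.25 = 3.11.

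The true marginal OR is 2.67, so benefit is overstated in this scenario.

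**The case against.** Adjusting only for the stratification factor is a valid and common choice. Randomization protects the comparison, and the test and interval already allow for chance imbalance. The trial meets its 80% target without the covariate, so the gain is a bonus. The adjusted repeat has an open list that could admit severity, and the contents of the imputation model may be set out in an analysis plan not shown. The power figures rest on assumed associations and on a single-time-point model, not the planned mixed model. The drop-out illustration needs severity to act in one arm only. Finally, the choice of Spence parent report over other scales is a judgement, and adjustment changes the conditional odds ratio.

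Most of this limits the size of the point. The sex-adjusted analysis is not invalid, 228 is not wrong, and the magnitudes are illustrative. Two things remain. The article itself fixes the primary model's covariates, and a severity term chosen later in a supplementary analysis would not change the primary estimate. The stated missing-data rationale also fails for the primary outcome whatever the strength of severity as a predictor, because that follows from eligibility alone.

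**Conclusion.** The point holds as an improvement that should be made. It is not an error that invalidates the trial. On the text, the primary model adjusts for sex only, the baseline diagnosis is constant, and a pre-randomization severity score goes unused for the outcome that most needs it.

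The power gain is about 1 to 8 percentage points over assumed ORs of 1.5 to 3.7 per SD, from an unadjusted level of about 83% to 86%. The possible drop-out bias (OR 2.67 moving to between 2.75 and 3.11) depends on an assumed severity-related drop-out pattern in the CBT arm and shows the direction of risk only. The finding that the baseline record is uninformative needs no such assumption, only that the model has its own baseline mean.

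**What to change.** - In the model that yields the 5-month primary estimate, add the baseline parent-reported Spence total as a continuous covariate alongside sex. Optionally add the number of baseline anxiety disorders from the entry interview.
- Include the same variables in the imputation model of the sensitivity analysis.
- Report the treatment effect standardised to a marginal risk difference and marginal odds ratio, next to the conditional odds ratio.
- Reword the missing-data rationale so that it does not claim a benefit from the baseline diagnosis for the primary outcome.

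The cost is one prespecified covariate already collected, a standardisation step and a few lines of text. No visit, measure or sample size changes. The conditional OR will differ from the 2.67 used in planning (about 2.75 to 3.29 for assumed ORs of 1.5 to 3 per SD), which is why the marginal effect should be reported too. The article describes data collection as ongoing, so the choice of score should be fixed and dated before outcomes by arm are seen.

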### Sample size

A Cochrane review reported on the efficacy of CBT for children and adolescents with anxiety disorders in the general population and found remission of anxiety diagnoses in 59% of CBT participants (*n* = 808) immediately post-intervention compared with 18% in controls (*n* = 542) [19]. Taking a conservative approach, we based our sample size on observing remission in 40% of the intervention group and 20% in the control group (odds ratio of 2.7) at 5 months post-randomization (approximates post-intervention point). In order to provide 80% power to detect this clinically meaningful difference, using a two sided test with alpha = 0.05 and accounting for 20% drop-out, we need to enrol 114 children in each arm (228 total children). This sample size will enable us to detect differences of 0.42 standard deviations (SDs) between the two groups with 80% power in the continuous secondary outcomes at 5 and 12 months (using a two-sided test with alpha = 0.05). Assuming that 10% of families opt out (based on our previous ADHD trials), 47% of those contacted are eligible, and 70% of those eligible consent to participate (based on our pilot study), we need to approach approximately 771 families in order to recruit the required sample of 228 children.

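### Neither the primary model nor the sample size allows for clustering of CBT children by psychologist, so standard errors are too small and 80% power is not assured if the therapist ICC is above 0

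*Protocol article*

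**What the plan says.** The Data analysis section of the protocol article sets one mixed model per outcome, analysed at child level and adjusted for gender, "using random effects to allow for the repeated measures within an individual". The random structure is spelled out by time point and contains no therapist term.

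Therapist appears once. It is an example in the list of baseline covariates for a repeated, adjusted analysis, to be used where appropriate.

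The Training and delivery section says that CBT is given to one family at a time by psychologists employed by the study, at three levels of qualification. The Randomization section keeps controls with their pediatrician.

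The Sample size section takes 40% against 20% remission, 80% power and two-sided alpha 0.05, and concludes: "accounting for 20% drop-out, we need to enrol 114 children in each arm". For the continuous outcomes it adds: "This sample size will enable us to detect differences of 0.42 standard deviations (SDs) between the two groups with 80% power". It mentions no caseload, ICC or design effect.

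**The concern.** Each psychologist treats several CBT children, and those children share whatever makes that psychologist more or less effective. Their outcomes are then positively correlated. Control children have no trial psychologist, so the correlation is in one arm only. A model with random effects only within the child treats all CBT children as independent and understates the variance of the CBT-arm mean.

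Two things are at stake. Confidence intervals and p-values for the primary and secondary outcomes would be too optimistic. The stated power would also hold only if psychologists did not differ at all.

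Listing therapist as a baseline covariate does not repair this. Therapist is assigned after randomization and is undefined for controls. Entered as an ordinary covariate, it is confounded with arm. If controls form their own level, the arm effect is not identified without an arbitrary constraint. If one psychologist is the reference, the arm effect becomes that psychologist against control.

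**Working it through.** **Inputs from the protocol (Sample size section):** 40% vs 20% remission, 80% power, two-sided alpha 0.05, 20% drop-out, 114 per arm, 0.42 SD.

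**Assumptions (not in the protocol):** number of psychologists k = 4 to 10; therapist ICC 0.02 to 0.10; equal caseloads; normal approximation.

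**1. Reproducing the stated figures**

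- Uncorrected n = [1.96·√(2·0.3·0.7) + 0.8416·√(0.4·0.6 + 0.2·0.8)]² / 0.2² = 81.2, so 82 per arm.
- With continuity correction: (81.2/4)·[1 + √(1 + 4/(81.2·0.2))]² = 90.9, so 91 per arm.
- Drop-out: 91/0.8 = 113.75, so 114 per arm, which matches. Without the correction it would be 82/0.8 = 102.5, so 103.
- Detectable difference: (1.96 + 0.8416)·√(2/91) = 0.415 SD (0.418 with the t distribution), which matches 0.42.

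Both figures are reached with no design effect, so neither contains an allowance for clustering.

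**2. Formulas with clustering in the CBT arm only**

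- Design effect: DE = 1 + (91/k − 1)·ICC.
- True SE over model SE: r = √((DE + 1)/2). The model SE is understated by 1 − 1/r.
- Type I error of the planned, unclustered test: 2·[1 − Φ(1.96/r)].
- Power of a test that allows for clustering: n₁ = 91/DE, n₂ = 91, with the pooled proportion weighted by n₁ and n₂. Power = Φ[(0.2 − c − 1.96·SE₀)/SE₁], where SE₀ is the pooled (null) and SE₁ the unpooled SE. Here c = 0 without continuity correction and c = (1/n₁ + 1/n₂)/2 with it.
- Detectable difference: 2.80·√((DE + 1)/91).

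**3. Numbers put in**

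Mild end (k = 10, ICC 0.02):
- DE = 1 + 8.1·0.02 = 1.162, and r = √1.081 = 1.040.
- n₁ = 78.3, SE₀ = 0.0701, SE₁ = 0.0694.
- Power without correction = Φ(0.90) = 82%.

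Severe end (k = 4, ICC 0.10):
- DE = 1 + 21.75·0.10 = 3.175, and r = √2.0875 = 1.445.
- n₁ = 28.7, SE₀ = 0.0925, SE₁ = 0.1007.
- Power without correction = Φ(0.19) = 57%.

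| k, ICC | DE | true/model SE | model SE too small by | type I, planned test | power, no correction | power, continuity-corrected | detectable SD |
|---|---|---|---|---|---|---|---|
| none | 1 | 1 | 0 | 5.0% | 84% | 80% | 0.415 |
| 10, 0.01 | 1.08 | 1.02 | 2% | 5.5% | 83% | 78% | 0.42 |
| 10, 0.02 | 1.16 | 1.04 | 4% | 5.9% | 82% | 77% | 0.43 |
| 8, 0.05 | 1.52 | 1.12 | 11% | 8.1% | 76% | 70% | 0.47 |
| 4, 0.10 | 3.18 | 1.45 | 31% | 17.5% | 57% | 48% | 0.60 |

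The type I column and the power columns describe different tests: the first is the planned analysis, the others a corrected one. Using a simple mean of the two proportions in SE₀ instead of the weighted one gives 53% instead of 57% at the severe end. Unequal caseloads, or a reference distribution that reflects few psychologists, would lower power further.

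**4. Effect of baseline data on the detectable difference**

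The 0.42 SD takes no credit for the baseline measure in the model. Assume a baseline correlation of 0.5, which multiplies child-level variance by 0.75. At k = 8 and ICC 0.05, 0.466 SD becomes 0.466·√0.75 = 0.40 if all variance shrinks. If the therapist part does not shrink, it becomes 2.80·√((2·0.75 + 0.519)/91) = 0.42. The primary outcome has no such gain, because every child has an anxiety diagnosis at entry.

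**The case against.** A reader might infer that the plan definitely fails to deliver 80% power and 0.42 SD. The documents do not support that, for four reasons.

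- The size depends on an ICC and a number of psychologists that are not given. At ICC 0.01 with 10 or more psychologists, the power loss is under 2 points.
- The 114 carries a continuity correction worth about 4 points. An uncorrected test that allows for clustering would still have 82% power at 10 psychologists and ICC 0.02.
- Baseline data may offset the loss for continuous outcomes, as shown above.
- A common clinician manual, shared training, fortnightly supervision, session checklists and coding of 20% of videos may keep differences between psychologists small. Individual-family sessions also rule out clustering by therapy group.

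The article does not say that therapist would enter as a fixed effect, and the coding may be left to an analysis plan that is not shown. A therapist variance estimated from perhaps four psychologists, inside a mixed logistic model that already has several random effects, may also be unstable.

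These points limit the size of the claim and the form of the remedy. They do not remove the omission. The primary model's random structure is stated and leaves therapist out. Extra precision from baseline data does not make an understated SE valid. Therapist is not a baseline covariate under any coding.

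**Conclusion.** The omission is certain: neither the primary model nor the sample size allows for therapist clustering, which exists in the CBT arm only, and the single listed use of therapist is unsuitable.

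The consequence is conditional. Any therapist ICC above 0 makes the model SEs too small. On the protocol's continuity-corrected basis, power is exactly 80% without clustering, so any positive ICC takes it below that. Over the assumed grid the effect runs from small to serious: type I error of about 5.9% to 17.5%, and power of 82% to 57% uncorrected or 77% to 48% corrected. The detectable difference is 0.43 to 0.60 SD before any gain from baseline data, so a shortfall against 0.42 SD is possible but not shown. The point should be addressed, mainly to protect the error rate of the primary result.

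**What to change.** - Remove therapist from the list of baseline covariates.
- For continuous outcomes, fit a partially nested model: a therapist random effect in the CBT arm only, each control child as its own cluster, and small-sample degrees of freedom.
- For the binary primary outcome, put the same term in the primary model. If psychologists are too few for stable estimation, prespecify it as a sensitivity analysis reported beside the primary result.
- Report the therapist ICC.
- Restate power and the detectable difference at the actual number of psychologists over a range of ICCs, for example 0.01 to 0.10. Do not enrol more children for this.

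The cost is one model term, one edited covariate list and one rewritten power statement. The downside is somewhat wider confidence intervals and a variance component estimated from few therapists.

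### With one diagnosis per child per visit, separate random effects at each time point leave the size of the primary odds ratio practically undetermined, though not its direction or its test

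*Protocol article*

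**What the plan says.** Under Data analysis, the protocol article plans one model per outcome: "a single mixed effects model will be fitted incorporating baseline, 5 month and 12 month data". It is adjusted for sex and has a treatment effect at each follow-up visit. The section then fixes the within-child structure: "These models will fit separate random effects and error terms at each time point". This applies to the primary outcome and to all secondary outcomes. For binary outcomes, "groups will be compared using mixed effects logistic regression, with results presented as odds ratios and their 95% confidence intervals" at 5 and 12 months.

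Four other statements matter here:

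- Measures and Table 2 give one parent diagnostic interview per child at each of baseline, 5 and 12 months.
- Participants and Inclusion/exclusion criteria require every child to have at least one of the three anxiety disorders at entry.
- Sample size plans on "observing remission in 40% of the intervention group and 20% in the control group (odds ratio of 2.7".
- The sensitivity analysis for the primary outcome is multiple imputation followed by ordinary logistic regression at 5 months.

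The article places no constraint on the random-effect variances. It does not say whether the primary OR is conditional on the child or population-averaged (marginal).

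**The concern.** A random effect and an error term can be told apart only if a child is observed more than once at the same time point. Here there is one value per child per outcome per visit.

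In a linear model, only the sum of the two variances at each visit can be estimated. In a logistic model there is no free error variance, and a visit-specific random effect acts on a single yes/no value. Its SD is then informed almost only by the assumed shape of the logistic-normal curve. The conditional log OR grows with that SD, so an SD that the data cannot pin down means an OR that the data cannot pin down.

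What is at stake is the headline estimate. The reported primary OR and its interval could be several times larger than the OR the trial was planned on, with no support from the data. It would also differ from the sensitivity analysis because of scale, and a reader could mistake that gap for an effect of missing data.

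**Working it through.** **1. The plan's own figures.** The Sample size section gives 40% and 20% remission, two-sided alpha 0.05, 80% power and 20% drop-out.

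- OR = (0.4/0.6)/(0.2/0.8) = 2.67, the stated 2.7. This is a marginal OR, since it compares group proportions.
- n per arm = [1.96·√(2·0.3·0.7) + 0.8416·√(0.4·0.6 + 0.2·0.8)]²/0.2² = (1.270 + 0.532)²/0.04 ≈ 81.2, so 82. With continuity correction this becomes 91, and 91/0.8 = 113.75, so 114. The plan's figure is reproduced, with 91 completers per arm.

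**2. Linear outcomes.** Three correlated random effects have 3 variances and 3 covariances. Three error variances bring the total to 9 parameters, for a 3×3 covariance matrix with 6 distinct elements. Only the total matrix is identified. The mean differences and their intervals depend on that total alone, so the split does not affect them.

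**3. Primary outcome, parameter count.** Baseline diagnosis is constant and carries no information. Ignoring sex, two arms × 3 free cell probabilities = 6, against 7 parameters (2 intercepts, 2 treatment effects, 2 SDs, 1 correlation). The plan adjusts for sex, which gives 2 × 2 × 3 = 12 free probabilities against 8 or 9 parameters. The count alone therefore does not settle the matter, and the likelihood has to be examined.

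**4. How the conditional OR depends on the SD.** For SD σ, solve ∫ expit(η + σz)φ(z)dz = p for p = 0.8 and p = 0.6 (proportions with the disorder). The difference in η is the conditional log OR. A rough check is log OR(conditional) ≈ 0.981·√(1 + 0.346σ²). At σ = 3 this is 0.981 × 2.03 = 1.99, an OR of 7.3, against 7.76 by integration.

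**5. Likelihood with sex included.** Expected counts were generated for 91 completers per arm at the planning rates. Assumed, because the article does not give them: 55% and 70% with the disorder at 12 months, 75% boys, a sex log OR of 0.4, and the true SD and correlation. Both SDs were then held at each value in the table and everything else was refitted.

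| SD held at | 5-month OR (remission) | Deviance change, true SD 2, correlation 0.7 | Deviance change, true SD 1, correlation 0.6 |
|---|---|---|---|
| 0.01 | 2.67 | 10.9 | 1.5 |
| 0.5 | 2.80 | 7.0 | 0.34 |
| 1 | 3.2 | 1.4 | 0 |
| 1.5 | 3.8 | 0.0004 | 0.0003 |
| 2 | 4.8 | 0 | 0.0007 |
| 3 | 7.8 | 0.0003 | 0.0012 |
| 4 | 13.1 | 0.0006 | 0.0014 |
| 5 | 22.8 | 0.0007 | 0.0017 |

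From SD 1.5 upward the fit is the same to the third decimal while the OR rises about sixfold (22.8/3.84 = 5.9). On the scale of having the disorder, the OR goes from 1/3.84 = 0.26 to 1/22.8 = 0.044.

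**6. Test and interval.** The Wald z for treatment at 5 months stays near 2.94 for every SD from 1 to 5. The standard error of the log OR is then log(OR)/2.94, and the 95% interval with the SD held fixed is:

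- SD 1.5: exp(1.345 ± 1.96 × 0.458), about 1.6 to 9.4.
- SD 5: exp(3.127 ± 1.96 × 1.064), about 2.8 to 183.

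**7. One shared random intercept.** Fitted to the same expected data, it changed the deviance by less than 0.001 and gave a single OR: about 3.7 in the first scenario and 2.9 in the second.

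**The case against.** The strongest reply is that this is one generic sentence in a condensed article covering linear, Poisson and logistic models. It may be loose wording for an unstructured covariance, and the full analysis plan may spell out the binary model. For linear outcomes that reading is reasonable and nothing of substance is lost. For the primary outcome it does not help. The article does not leave the structure open; it prescribes one that a single binary value per visit cannot support.

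A second reply is that the SDs in the table were set by hand, up to 5, and not estimated. That is fair. An OR of 23 is the end of a grid and not a forecast, and the association between the 5- and 12-month diagnoses does rule out small SDs in the first scenario. The table shows only that the data cannot choose among the larger values.

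A third is that the planned sensitivity analysis gives an identified 5-month OR and would expose an inflated primary one. This is true, but it is labelled as sensitivity and is on a different scale.

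A reader might infer more than the documents support:

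- *That the OR could take almost any value.* It cannot fall below the marginal OR (2.67 at planning rates), reach 1 or change direction.
- *That the test of the primary hypothesis is arbitrary.* The z statistic hardly moves.
- *That the continuous secondary results are unsound.* Their mean differences rest on the identified total covariance.
- *That counting parameters proves non-identifiability.* With sex in the model it does not; the flat likelihood does the work.

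**Conclusion.** The point holds for the size of the primary odds ratio and its confidence interval. As written, the primary model leaves the visit-specific random-effect SDs practically unidentified. Over SDs of 1.5 to 5 the conditional 5-month OR for remission runs from about 3.8 to 23 with a deviance change below 0.002, against a marginal 2.67 at the planning rates. Which value is reported would depend on software constraints or starting values. It would not be comparable with the planning OR or with the sensitivity analysis.

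The point does not extend to the direction of the effect, to the treatment test, or to the mean differences for linear outcomes, where only the wording needs correcting.

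The figures rest on the assumed 12-month rates, sex distribution and effect, and true SDs and correlations. The flatness appeared in both scenarios tried. Where it begins varies: from SD 1 when the true SD is 1, and from about 1.5 when the true SD is 2 with the stronger association between visits.

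**What to change.** Delete the phrase about separate random effects and error terms, and specify by outcome type:

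- **Continuous:** an unstructured 3×3 within-child covariance with no added random effects. The treatment effects at 5 and 12 months stay as planned.
- **Binary, including the primary:** report a marginal 5-month OR. The simplest route is to make the planned multiple imputation with logistic regression the primary analysis; GEE on multiply imputed data is an alternative. Alternatively, keep a mixed logistic model with one shared random intercept, state that its OR is conditional, and report a standardised marginal OR beside it.
- **Count:** leave any overdispersion term in place. In a Poisson model a random effect per observation can be estimated and is useful.

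The replacement must keep the plan's provision for loss to follow-up, set at 20% in the Sample size section. Unweighted GEE without imputation generally needs a stronger missing-data assumption, and a complete-case logistic model drops children without a 5-month interview. Imputation should therefore accompany either, using the 12-month diagnosis where it is available.

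The cost is a few sentences and slightly more analysis work, with no change to data collection or sample size. The marginal OR will be smaller than a conditional one, but it is on the scale on which the trial was planned.
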